## Methods/design

### Study design

A two-armed, pre-post test, clustered randomized control trial (CRCT) design will be used in this study. Figure 1 shows the overall design. The data will be collected at three time points: T_0_, baseline; T_1_, 3 months after the completion of an 8-week intervention; and T_2_, 6 months after the intervention.

**Fig. 1 Fig1:**
[figure not shown]
Study design

### Participants

The participants, firefighting teams’ members from the Hong Kong Fire Service Department (HKFSD), will be recruited from fire stations during their free time by the distribution of promotional pamphlets to firefighters in their corresponding fire stations through their fire station colleagues. When a potential participant expresses his interest to participate in this study, he will receive a detailed information sheet (Additional file 1), consent form (Additional file 2) and baseline questionnaire (Additional file 3). Each fire station will be treated as an individual cluster.

### Inclusion criteria

Inclusion criteria will be: (1) male; (2) aged 18 years or older; (3) currently working for the HKFSD as firefighter, working on “24 hours on, 48 hours off” shift; and (4) ownerof smartphone with Internet access. Firefighters who are participating in any other relevant health promotion programmes at the time of the study will be excluded. Written informed consent (Additional file 2) will be obtained from each participant. In order to avoid interference or contamination of data, all participants will be reminded not to disclose any information which they have received from the researcher, and this reminder will be stated in the consent form.

### Recruitment

The participants will be recruited from more than one fire station, located in different districts in Hong Kong. Convenience and snowball sampling methods will be used for the recruitment. The associated participants will be assigned randomly into either intervention or control groups. All the associated participants will be blinded to their intervention allocation.

### Sample size

There are no clear definitions or guidelines for estimating the sample size for a feasibility study [98]. According to [99], a sample size of 10–15 in a group will probably be sufficient. The proposed sample size was calculated to be 38, allowing for an estimation of the feasibility proportions of adherence and retention to within at least ±17% [100, 101] using a 95% confidence interval with a power of 80% to detect an effect size of 0.6 [77]. The main purposes of this exploratory feasibility study are to collect data to allow the design and sample size calculation for the CRCT.

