### Study aims

This study has two aims. The first is to determine the feasibility of using a TTM-based printed promotion pamphlet and delivering it with stage-matched teaching materials through WhatsApp to promote healthy eating. The second is to evaluate the potential effects of WhatsApp as a vehicle to promote healthy eating habits in firefighters in Hong Kong. The desired primary outcome is changed eating habits, while the secondary outcomes are body mass index (BMI) and waist-to-hip ratio (WHR).

The following research questions have been set: (1) Will the use of the TTM-based promotion pamphlet and WhatsApp bring about greater changes in their eating habits than the use of the TTM-based pamphlet alone? (2) Will the use of the TTM-based promotion pamphlet and WhatsApp lead to greater changes in the firefighters’ BMIs than the use of the TTM-based pamphlet alone? (3) Will the use of the TTM-based promotion pamphlet and WhatsApp change the firefighters’ WHRs more than the use of the TTM-based pamphlet alone?

In order to address two of the “areas of focus” of a feasibility study (Implementation and Practicality), two more research questions have been posed: If the use of WhatsApp helps to improve firefighters’ eating habits, will this also reduce their BMIs and WHRs and increase their fruit and vegetable intake? Will firefighters find this intervention more useful and efficient than the TTM-based promotion pamphlet?

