### Data analysis

All of the collected data will be cleaned prior to the analysis process. The data analysis will be conducted by a statistician who is blind to the participants’ group allocation. The participants’ demographic characteristics will be presented using descriptive statistics (mean and standard deviation) for the continuous data, including age, body height and weight plus BMI, and percentage frequencies for the categorical data, including gender, marital status and educational level. Inter-relationships between the variables will be assessed using Pearson’s correlation coefficient. Differences between the intervention and control groups on outcome indicators will be compared using *t* tests and chi-square tests for the continuous and categorical data respectively. The effect of time (baseline; 3 and 6 months after the completion of the programme) on the outcome measurements will be investigated using repeated measures analysis of variance (ANOVA). The impact of “baseline stage matching” on “stage of change” and other outcome measures within the intervention group will be compared using the Kruskal-Wallis *H* test and one-way ANOVA. Normality tests will be conducted. If the data are normally distributed, it will be appropriate to use parametric tests such as one-way ANOVA. But if they are not normally distributed, non-parametric tests such as the Kruskal-Wallis *H* test will be used. *P* values of less than 0.01 will be considered as statistically significant for all comparisons. All statistical analyses will be conducted using SPSS version 22.0. Intention-to-treat analyses will be applied. As of now, there is no clear cut-off for the acceptable proportion of missing data in a dataset for statistical data analysis. Questionnaires with missing rates of more than 10% will be regarded as “disqualified” and excluded from the analysis. Various statistical methods will be used to treat missing data, including replacement by means or values from the regression analyses, depending on the amount and type of missing data.

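### The stated 80% power for an effect size of 0.6 with 38 participants is not delivered for a two-sided between-arm comparison, whether 38 is the total or the number per arm

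*Protocol article*

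**What the plan says.** The Sample size section gives two justifications in one sentence. The first is precision: "The proposed sample size was calculated to be 38, allowing for an estimation of the feasibility proportions of adherence and retention" to within ±17%. The second is power: "using a 95% confidence interval with a power of 80% to detect an effect size of 0.6". The section does not say whether 38 is the total or the number per arm, which test is meant, what kind of effect size 0.6 is, or whether the test is one- or two-sided. It mentions no design effect.

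Study aims states that "The desired primary outcome is changed eating habits", and its three numbered questions all ask whether pamphlet plus WhatsApp does better than the pamphlet alone. Data analysis compares the two groups with t tests for continuous outcomes and sets the threshold: P "values of less than 0.01 will be considered as statistically significant for all comparisons". Participants and Randomization make the fire station the cluster and the unit that is allocated.

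**The concern.** A statement of 80% power tells readers how to interpret a null result. If the true power is well below that, a non-significant difference could be taken as fairly strong evidence against adding WhatsApp, when the study would often have missed a real effect of the size named.

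Three features of the text raise doubt. Thirty-eight is small for a two-arm comparison at 0.6 standard deviations. The power clause is tied to a 95% interval, while the analysis tests at 0.01. The trial is cluster-randomised, but the sentence states no allowance for that. The section also says the data will inform the sample size of the later trial, so an unsupported power statement could carry forward.

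**Working it through.** **Inputs.** From Sample size: n = 38, power 80%, effect size 0.6, 95% interval (alpha 0.05), precision ±17%. From Data analysis: alpha 0.01 for all comparisons and t tests between groups. Assumed, because the article does not say: 0.6 is a standardised mean difference d between arms, the test is two-sided, and allocation is 1:1.

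**1. Precision, the plan's own figure.** Half-width = 1.96 × √(p(1−p)/n), at p = 0.5.
- n = 38: 1.96 × √(0.25/38) = 15.9%.
- n needed for 17%: 1.96² × 0.25 / 0.17² = 33.2, so 34, which gives 16.8%.
- If a 10% loss is assumed (the article does not state one), 34/0.9 = 37.8, so 38.

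The precision justification for 38 reproduces.

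**2. Power, no clustering.** Two-sample t test with noncentrality d × √(n per arm / 2).
- 19 per arm: 0.6 × √9.5 = 1.849 on 36 degrees of freedom. The critical value is 2.028 at 0.05 and 2.719 at 0.01.
- 38 per arm: 0.6 × √19 = 2.615 on 74 degrees of freedom. The critical value is 1.993 at 0.05 and 2.644 at 0.01.

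| Reading of 38 | Power at 0.05 | Power at 0.01 |
|---|---|---|
| Total (19 per arm) | 43.7% | 20.9% |
| Per arm | 73.3% | 49.2% |

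Neither row gives 80% at either threshold.

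**3. Number needed for 80%.** The normal approximation is n per arm = 2(z₁₋α/₂ + z₀.₈)²/0.6².
- Alpha 0.05: 2 × (1.960 + 0.842)²/0.36 = 43.6, so 44. The exact t test needs 45 per arm (90 in total).
- Alpha 0.01: 2 × (2.576 + 0.842)²/0.36 = 64.9, so 65. The exact t test needs 67 per arm (134 in total).

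With 19 per arm, the difference detectable at 80% power is 0.93 SD at 0.05 and 1.16 SD at 0.01.

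**4. Clustering.** The Sample size section gives no ICC and no cluster size, so this step is a range over assumptions. With ICC from 0.01 to 0.10 and 5 to 10 men per station, the design effect 1 + (m−1) × ICC runs from 1 + 4 × 0.01 = 1.04 to 1 + 9 × 0.10 = 1.9. The effective number per arm then falls from 19 to between 19/1.04 = 18.3 and 19/1.9 = 10.0. The t-test power becomes about 42% to 25% at 0.05 and 20% to 9% at 0.01. This is still favourable, because it does not charge for the few degrees of freedom that a small number of stations would leave.

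**5. Readings that would reach 80%.**
- One-sided 5%, two arms, 38 per arm: 82.8%.
- One-sided 5%, pre-post within one group of 19: 80.8%.
- Two-sided pre-post on all 38: 95.0% at 0.05 and 83.0% at 0.01.
- 0.6 read as Cohen's f (d = 1.2), 19 per arm: 94.9% at 0.05 and 82.9% at 0.01.
- Baseline-adjusted comparison, 19 per arm: 80% needs 1 − ρ² = 19/44 = 0.432, so a baseline correlation ρ of about 0.75 at 0.05. At 0.01 it needs 1 − ρ² = 19/65 = 0.292, so ρ of about 0.84.

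The article states none of these.

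**The case against.** The best defence is that the clause is under-specified, so it cannot be called wrong. The source of the 0.6 is not available here, and step 5 shows readings on which 80% is met. Part of this stands. The figures of 44% and 21% are conditional on 38 being the total and 0.6 being a between-arm standardised difference, and they should not be quoted without those conditions. It would also be wrong to infer that 38 can only have come from a paired comparison, because a one-sided 5% two-arm test with 38 per arm also passes 80%. The defence does not rescue the clause, however. The one-sided readings sit badly with a 95% interval, the within-group readings do not answer the numbered research questions, and the Cohen's f and baseline-adjusted readings need information the article does not give.

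A second defence is that this is an exploratory feasibility study whose size rests on precision. That stands as a limit on severity. A feasibility study needs no power claim, but one that is made should be correct.

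Three stronger readings are tempting, and the document does not support them.
- A reader might infer that the ±17% precision fails for adherence, because WhatsApp messages go only to the intervention arm. The article does not define adherence, and both arms receive the pamphlet, questionnaire and measurements. For all 38 the target is met. The point holds only if WhatsApp adherence is meant, and then at p = 0.5; with 19 people the half-width is already 16.9% at p = 0.83.
- A reader might infer that adherence and retention will not be reported, because Data analysis does not mention them. A condensed article may leave that to the full protocol or analysis plan, so silence here shows nothing.
- A reader might infer that the primary outcome must be changed to the feasibility proportions. Correcting one power clause does not require it.

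**Conclusion.** The power clause is wrong as written for the comparison the trial sets out to make. Under a two-sided t test with d = 0.6 and no clustering, power is about 44% (0.05) or 21% (0.01) if 38 is the total, and about 73% or 49% if 38 is per arm. With 19 per arm and assumed design effects of 1.04 to 1.9, it falls to roughly 42% to 25% at 0.05 and 20% to 9% at 0.01. The 95% interval in Sample size and the 0.01 threshold in Data analysis also disagree and need reconciling.

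The fault is confined to the power statement. The precision basis for 38 is sound before any design effect. Given that and the exploratory purpose, this is a should-fix.

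**What to change.** Keep 38 and its precision rationale, stated as ±15.9% at p = 0.5 for all 38 and ±16.8% for 34 completers, before any design effect.

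Delete the clause claiming 80% power for an effect size of 0.6. Alternatively, replace it with the power actually obtained, naming the test, the number per arm, the definition of the effect size, one alpha reconciled between Sample size and Data analysis, and the allowance for clustering.

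Interpret between-arm effects as estimates with 95% confidence intervals, so that a null result is not read as 80%-powered evidence of no effect. If adherence means adherence to the WhatsApp programme, give its precision on the intervention-arm denominator: 1.96 × √(0.25/19), about ±22% at p = 0.5 with 19 people.

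The cost is rewording. No extra participants are needed. Recruitment has already closed according to Trial status, so the correction governs how the results are reported and read. The stated figures become less favourable.

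### The stated 80% power for an effect size of 0.6 is not delivered by 38 men in the planned between-arm t test: about 44% at two-sided 5% if 38 is the total, about 73% if it is per arm

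*Protocol article*

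**What the plan says.** The Sample size section of the protocol article states "The proposed sample size was calculated to be 38". It supports that number first by the margin of error on adherence and retention (±17%), and then by power: "using a 95% confidence interval with a power of 80% to detect an effect size of 0.6 [77". Just before, it cites a rule of thumb, "a sample size of 10–15 in a group will probably be sufficient". The section does not name the test, the type of effect size, the sidedness or the allocation ratio, and it does not say whether 38 is a total or a number per arm.

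Under Study aims, the research questions on eating habits, BMI and waist-to-hip ratio all ask whether pamphlet plus WhatsApp changes more than pamphlet alone. The Data analysis section takes these up: "Differences between the intervention and control groups on outcome indicators will be compared using" t tests for continuous data and chi-square tests for categorical data. It then sets the threshold: P "values of less than 0.01 will be considered as statistically significant for all comparisons".

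**The concern.** One number carries two justifications, and they need not agree. A sample chosen for a ±17% margin on a proportion has no built-in power for a mean difference of 0.6 between two arms. An effect of that size usually needs well over 38 men for 80% power, so the power clause looked as if it had been attached to a number reached another way.

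At stake is how the arm comparison is read. A reader who accepts 80% power for 0.6 may take a non-significant difference as fair evidence that no such effect exists. The Sample size section says that the data will inform the design and size of a later cluster trial, so the misreading could carry forward.

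This is separate from the gap between the 5% implied by "using a 95% confidence interval" and the 0.01 used in the analysis. The power figure already fails at 5%, so aligning the two thresholds would not repair it.

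**Working it through.** **Inputs.** From the Sample size section: n = 38, effect size 0.6, power 80%, and 5% as implied by the 95% interval. From Data analysis: t test between arms, threshold 0.01. Assumed because not stated: 0.6 is a standardised mean difference d, 1:1 allocation, two-sided test, no drop-out, no clustering. Equal arms, full retention and no clustering all favour the plan.

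**Step 1: the precision figure.** Half-width = 1.96 × √(p(1−p)/n), largest at p = 0.5.
- n = 38: 1.96 × √(0.25/38) = 0.159.
- Exact (Clopper-Pearson) interval for 19/38: 0.334 to 0.666, half-width 0.166.
- n needed for ±17%: 1.96² × 0.25/0.17² = 33.2, so 34. With an assumed 10% loss, 34/0.9 = 37.8, so 38.

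The ±17% is met by 38 in total.

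**Step 2: the power figure.** For n men per arm, the t statistic has 2n − 2 degrees of freedom and noncentrality d × √(n/2).
- 19 per arm: 0.6 × √9.5 = 1.849, on 36 df. Critical values are 2.028 (5%) and 2.719 (1%).
- 38 per arm: 0.6 × √19 = 2.615, on 74 df. Critical values are 1.993 (5%) and 2.644 (1%).

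| Reading of 38 | Two-sided 5% | Two-sided 1% | One-sided 5% |
|---|---|---|---|
| Total (19 per arm) | 43.7% | 20.9% | 56.7% |
| Per arm | 73.3% | 49.2% | 82.8% |

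The total reading fits the cited 10 to 15 per group better.

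**Step 3: what 80% would take.** For d = 0.6, two-sided: 45 per arm (90 in total) at 5%, or 67 per arm (134 in total) at 1%. With 19 per arm, 80% power is reached only for d of about 0.93 at 5% and about 1.16 at 1%.

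**Step 4: other routes to 80%.**
- One-sided paired t test within one arm of 19: 80.8%, and 2 × 19 = 38.
- Within-person contrast in all 38 men: 95.0% at two-sided 5%, 83.0% at two-sided 1%.
- Baseline-adjusted comparison of arms: needs a correlation of √(1 − (0.6/0.934)²) = 0.77 between baseline and follow-up. No such analysis is stated, and the questionnaire's mean two-week retest agreement is 0.75.
- Between-arm effect averaged over repeated measures (normal approximation, within-person correlation 0.3 to 0.7): about 52% to 72%.
- 0.6 read as Cohen's f (two groups) or w (1 df), N = 38, 5%: about 95% and 96%.

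**Step 5: clustering.** Fire stations are randomised, so the design effect is 1 + (m − 1) × ICC for m men per station. The article gives neither value. Over an assumed ICC of 0.01 to 0.10 and m of 5 to 19, power with 38 in total at 5% runs from 44% down to 20% (normal approximation, which gives 45.6% without clustering).

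**Step 6: precision of the arm difference.** The 95% half-width with 19 per arm is 2.028 × √(2/19) = 0.66 SD, before clustering.

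**The case against.** The strongest reply is that the Sample size section does not tie the 80% to the between-arm t test, and that 0.6 comes from a cited source that is not at hand. Three calculations do reach about 80% or slightly more: a one-sided paired test in 19 men, a within-person contrast in all 38 at 1%, and a one-sided test with 38 per arm. The plan also includes a repeated measures ANOVA for the effect of time. It would therefore be too strong to say that no analysis of 38 men can have 80% power for 0.6.

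That part stands, but it does not rescue the statement. The one-sided routes are not stated, and within-person tests do not answer the between-arm questions under Study aims. Reading 0.6 as f or w gives 95% or more, so it does not explain the 80% either.

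The objection also rightly limits two stronger readings. A reader might infer that a true effect of 0.6 would be missed more often than found. That holds for 38 in total with a two-sided 5% test, but not for 38 per arm at 5% (73%) nor for a one-sided test of 38 in total (57%). A reader might also infer that the authors will treat a null result as proof of no effect. Nothing in the article says so, and it describes the study as exploratory, with feasibility as the first aim.

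**Conclusion.** The power statement is wrong as written for the planned between-arm t test. Power at two-sided 5% is about 44% if 38 is the total and about 73% if it is per arm; at the threshold the protocol actually sets, it is about 21% and 49%. These figures assume a standardised mean difference, equal arms, no drop-out and no allowance for fire stations. Neither reading of 38 reaches 80% with a two-sided test, so the conclusion does not depend on which reading is right; the exact figure does.

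It does not follow that the trial is wrongly sized or should have enrolled 90. The ±17% basis supports 38 in total, and the article presents the study as a source of design data for a later trial. The fault lies in a claim the study did not need to make, so severity is moderate.

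**What to change.** Keep 38 on the precision basis and delete "with a power of 80% to detect an effect size of 0.6". This is the preferred change.

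If a power figure is kept, say whether 38 is the total, name the test, the type of effect size, the sidedness and the allocation ratio, and give the figure at the threshold actually used. For 19 per arm, two-sided:
- at 5%, power for 0.6 is about 44%, with 80% reached only for about 0.93;
- at 1%, power for 0.6 is about 21%, with 80% reached only for about 1.16;
- both powers fall further once fire stations are allowed for.

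Quoting the 5% figure alone would still overstate power while the analysis tests at 0.01.

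Report arm differences as estimates with confidence intervals (95% half-width about 0.66 SD before clustering), and do not read a non-significant result as evidence of no effect.

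The cost is one sentence of wording, or a less favourable stated figure, and no extra participants. The Trial status section gives recruitment as finished and completion on 29 February 2020, so correcting the wording and the interpretation is what remains open.

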### Teaching materials

The teaching material content has already been designed on the basis of three sources: Promoting Healthy Lifestyles: Alternative Models’ Effects (PHLAME) [102], the Centre for Food Safety [103] and the Department of Health in Hong Kong [104]. In order to design an intervention on healthy eating which would be suitable for Hong Kong firefighters, existing information about healthy eating education and four out of ten sessions which focused on healthy eating from PHLAME have been modified. The teaching materials focus on (1) the rationales for healthy eating; (2) the advantages of consuming fruit and vegetables; (3) understanding methods of cooking fruit and vegetables; and (4) practical tips for getting enough fruit and vegetables when eating out and during festival seasons. The TTM was also designed to assess each intervention participant’s “stage of change”. The TTM includes four core constructs: stages of change, processes of change, decisional balance and self-efficacy [105]. In formulating this intervention, guidelines such as goals, processes of change, strategies and health promotion information (HPI) given through WhatsApp were set with reference to those developed by Lee et al. (2017) to support the application of TTM to promote healthy eating [106]. These teaching materials will be delivered to the participants in the intervention group through WhatsApp.

### Development of pamphlet

The contents of the pamphlet will be the same as the teaching material, as described above. All participants will receive all stages of the intervention, regardless of which stage they belong to at the baseline.

